### **8.3. Format and timing of outcome measures**

All women with early onset pre-eclampsia will be admitted into hospital until child-birth, enabling baseline and follow-up data to be collected directly from hospital notes onto the StAmP data collection forms and the online trial database. The local PI, nominated investigators or research midwives will be responsible for data collection and entry on to the database.

The baseline clinical measurements will be those taken most immediately prior to randomisation and used to diagnose pre-eclampsia and determine the severity of the condition.

All daily biochemical, haematological and clinical measurements, concomitant medications, fetal assessments and indicators of maternal morbidity will be collected on StAmP data collection forms to ensure important events are recorded and to determine which events or reactions should be reported as serious adverse events or suspected unexpected serious adverse reactions.

On the day of birth of the baby, neonatal outcomes will be recorded. Appropriate data collection forms will be completed until discharge.

The final time-point is at 6 weeks post-partum. An out-patient appointment with the investigator and/or local PI and ideally the research midwife will be made as close to this time-point as possible. Post-partum data collection forms will be used to collect secondary outcome measurements from maternal and neonatal notes and any additional information direct from the parents. A final additional blood sample will be required for biomarker assay.

#### **8.3.1. Biomarker assessment**

The biomarkers (sFlt-1, PlGF and sEng) will be assayed in a central laboratory at Aston University.

#### **8.3.2. Clinical outcomes**

When taking blood pressure, the woman should be rested and sitting. The blood pressure cuff should be of the appropriate size for the woman's arm and should be placed at the level of the heart. Korotkoff phase 5 is the appropriate measurement of diastolic blood pressure (55). Only sphygmomanometers validated for use in pregnancy will be used.

Biochemical and haematological measurements should be collected as part of routine clinical practice at each centre. Reference ranges for each centre's laboratory will be collected at the start of recruitment and centres should notify the StAmP Trial Office of any changes to these references.

#### **8.3.3. Data collection and trial database**

Data should be collated directly from the mother or from the mother's hospital notes by using the StAmP data collection forms. These will form the source data. Data should be entered on to the secure online StAmP database as soon as possible after collection by the research midwife, investigator or local PI, who will be allocated personal usernames and passwords that restrict access to participants at their centre. Alternatively, paper forms can be sent to the StAmP Trial Office for central input. Data validation is built into the online database, so that range, date and logic checks are performed at the point of data entry. Email and letter reminders will be sent to the investigator and research midwife for missing data forms, missing data or data inconsistencies.

### **8.4. Withdrawal from treatment or follow-up**

Withdrawal from follow-up is the decision of the participant. However, withdrawn patients can bias clinical trial results and reduce the power of the trial to detect important differences, so women should be encouraged to allow data collection to continue even if trial treatment ceases. If a participant wishes to withdraw from follow-up and/ or treatment, there will be a checklist to guide investigators as to what to do

with data, drug treatment packs and samples. To reduce loss to follow-up, we shall record mother's NHS number, which will allow us to track participants via their GP practice.

### **8.5. Long-term follow-up**

The developmental function of the infants born to participants in the StAmP Trial is of interest but outside the scope and time-frame for the Trial as it currently stands. Should further funding become available, a new observational protocol will be developed, approval gained and participants traced through the randomising centre and the mother's NHS number.

### **8.6. Definition of the End of Trial**

The interventional phase of the trial will end when the last participant has delivered her baby. The observational phase of the trial will cease when the 6 week follow-up has been completed for the last participant recruited.

### **8.7. Confidentiality of personal data**

Personal data and sensitive information required for the StAmP Trial will be collected directly from trial participants and hospital notes. Participants will be informed about the transfer of this information to the StAmP trial office at the BCTU and asked for their consent. The data will be entered onto a secure computer database, either directly via the internet using secure socket layer encryption technology or indirectly from paper by BCTU staff. Biological samples, which have been transferred from local centres to the central laboratory, will only be identified by their trial number. Central laboratory staff will not have access to personal data.

All personal information received in paper format for the trial will be held securely and treated as strictly confidential according to BCTU policies. All staff involved in the StAmP Trial (clinical, academic, BCTU) share the same duty of care to prevent unauthorised disclosure of personal information. No data that could be used to identify an individual will be published. Data will be stored on a secure server at Birmingham Clinical Trials Unit (BCTU) under the provisions of the Data Protection Act and/or applicable laws and regulations.

### **8.8. Long-term storage of data**

After the end of the trial, the site files from each centre will be collected and incorporated into the trial master file held by the BCTU.

In line with the Medicines for Human Use (Clinical Trials) Regulations, once data collection is complete on all participants, all data will be stored for at least 5 years (but ideally not less than 15 years). This will allow adequate time for review and reappraisal, and in particular with the StAmP trial, form the basis for further follow-up research. Any queries or concerns about the data, conduct or conclusions of the trial can also be resolved in this time. Limited data on the participants and records of any adverse events may be kept for longer if recommended by an independent advisory board.

Trial data will be stored within the BCTU under controlled conditions for at least 3 years after closure. Long-term offsite data archiving facilities will be considered for storage after this time. The BCTU has standard processes for both hard copy and computer database legacy archiving.

## **9. ACCRUAL AND ANALYSIS**

### **9.1. Sample size**

The sample size for this trial has been estimated using the hypothesis that statins will reduce sFlt-1 levels compared with placebo during the first 72 hours after onset of treatment. We have demonstrated that

statins inhibit sFlt-1 from  $18.0 \pm 0.4$  ng/ml to  $8.5 \pm 1.2$  ng/ml (mean  $\pm$  SD) within 24 hours in an *ex vivo* human placental model (34;56).

The level of sFlt-1 in a normal pregnant woman is  $19.3 \pm 15.5$  ng/ml and for those with pre-eclampsia around  $66.6 \pm 26.4$  ng/ml. Our studies suggest that with statin use sFlt-1 levels will be expected to halve, a reduction of over one standard deviation. To detect one standard deviation difference with 80% power and  $p < 0.05$  would require 34 patients in total at any one time point. For our primary analysis we shall be carrying out a repeated measures analysis assessing the effect over the first three days (1 reading available per day), including an adjustment for the baseline value. If we conservatively assume that the Intra-class Correlation Coefficient of these readings is 0.9, and additionally that the correlation with the baseline value is only 0.1, then the required sample size for this analysis is 32.

To allow for some women failing to provide all three days of sFlt-1 data, StAmP will aim to recruit **up to 64** participants in total.

## **9.2. Statistical Analysis**

The primary outcome measure of sFlt-1 during the first three days will be analysed using a repeated measures analysis in SAS PROC MIXED, including the baseline value as a covariate. For the primary analysis the treatment effect will be considered constant over time, secondary analyses will examine the possibility of a trend over time. Plots of mean score over time will be shown for clarification.

As a secondary analysis sFlt-1 and the sFlt-1/PIGF ratio over, initially, the first 14 days and latterly all available data will be analysed using a repeated measures analysis in SAS PROC MIXED. Parameters allowing for treatment arm, time and baseline value will be included in the model. Initially, the treatment effect will be assumed to be constant over time, but if time by treatment interaction is shown to be important by including this parameter in the model (the conventional level of  $p = 0.05$  will be used here) then further investigation into effects at differing time points will be made by analysing the least-square means as above. Plots of mean score over time will be shown for clarification.

The length of gestation (to delivery) post randomisation will be analysed using a Cox Proportional Hazards model. Hazard ratios will be calculated. Kaplan-Meier plots will be produced.

All other continuous measures (clinical measures, etc) will be considered in the same manner as above (adjusting by baseline value if available). Dichotomous outcomes (mortality, etc) will be presented as risk ratios, with a corresponding chi-squared test performed. The latter will be analysed using SAS PROC GENMOD.

Apart from baseline value, no adjustments for covariates will be made in the first instance in any of the investigations above as good balance is expected between groups due to the minimisation procedure at randomisation.

All analysis will be by intention-to-treat, whereby patients will be analysed according to the arm they were randomised to regardless of whether they complied with the treatment. All tests are 2-sided and results will be presented as a point estimate along with 95% confidence intervals. All analyses will be conducted by the trial statistician at the BCTU. A comprehensive Statistical Analysis Plan will be drawn up prior to any analysis and will provide further details on the proposed analysis.

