## **2.4. The choice of questions to be asked**

### **2.4.1. Rationale**

The rationale for using statins to ameliorate pre-eclampsia is based on in vitro work that identifies a consistent activation of heme-oxygenase and suppression of sFlt-1 and sEng (anti-angiogenic factors elevated in pre-eclampsia) in cultured endothelial and trophoblast cells (34). For this reason we have chosen to use a measure of circulating maternal serum levels of sFlt-1 and sEng as primary endpoints. This trial is not powered to look at changes in clinical outcome, but differences in the length of pregnancy after randomisation will be used to inform the Data Monitoring Committee as to whether statins are clinically harmful.

The safety of statins in pregnancy is uncertain. Limited evidence on 550 women who inadvertently took statins in the first trimester shows no higher level of fetal abnormality than in the general population (see above). However 3 cases of VACTERL syndrome (out of 550), which is normally found in only 1:3500 pregnancies, raises suspicions that statins may interfere with midline development to cause this anomaly during the first trimester. We have chosen to limit this study to women with pre-eclampsia after 24 weeks gestation, away from the first trimester. There have been very few documented cases of women who have continued statins into the second and third trimesters, but there are no cases associated with fetal harm. Furthermore, we have chosen to study the effect of pravastatin, a hydrophilic statin, that unlike the other lipophilic statins will cross the placenta much less easily. There have been no reported cases of fetal harm out of 32 cases in which the mother took pravastatin in pregnancy.

**Early severe pre-eclampsia (24 to 31+6 weeks gestation) is a life-threatening condition for mother and offspring. Although we have minimised the risks to the fetus by studying women after 24 weeks gestation and using hydrophilic pravastatin, we feel the potential harm to the fetus of early severe pre-eclampsia is balanced by the potential benefits of identifying a disease-modifying drug.**

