#### **6.2.2. Route of administration, dosage, dosage regimen and treatment period**

At randomisation, a bottle number is provided and this will correspond to a drug treatment pack available in the hospital pharmacy. The pharmacist will receive notification of the name, trial number, and bottle number of the randomised woman and will prepare the drug treatment pack for dispensing. The treatment pack will contain 28 capsules for use by one participant.

A single capsule must be taken as once daily in the evening, orally with or without food. On the day of randomisation, the first dose should be given that evening. If a patient is randomised too late in the evening, the first dose may be given the following evening. Treatment should continue daily in the evening until the pregnancy is ended.

The pharmacist should keep accurate records of trial drugs dispensed using a pharmacy log provided by the StAmP Trial Office. The attending clinician administering the treatment will also be required to record each dose on the trial drug chart. Trial drugs must be kept in the packaging supplied and under no circumstances used for other participants or non-participants.

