## **6.6. Sample collection**

### **6.6.1. Blood sample collection**

Blood samples of 5-10mls will be collected for the analysis of inflammatory and anti-angiogenic factors including s-Flt-1, PlGF, and sENG. As a minimum, samples need to be collected daily at baseline, on days 1-3 of the trial treatment period and twice a week thereafter until discharge from hospital post-delivery. Blood samples should be taken at the same time as routine sampling wherever possible, however where this is not possible, additional samples may occasionally need to be taken specifically for the trial. All samples should be spun down and plasma collected. The plasma sample tube should be labelled with a pre-printed label containing StAmP Trial Number, sample day and type. Patient initials, date of birth and date of sample should be written on the label. Samples will be stored in a -80°C freezer (or -20°C if not available) within a StAmP sample storage box, until the mother has completed her involvement in the trial.

Once the mother has completed her involvement in the trial (after the 6-week post-partum blood sample collection), all tubes should be sealed and sent to Aston University as and when instructed by the StAmP Trial Office.

The StAmP Trial Office will send out instructions on sample preparation, freezing and transport guidelines to all participating centres.

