## 8. OUTCOME MEASURES

### 8.1. Primary outcome measure

The primary outcome measure will be the effect of pravastatin on maternal serum sFlt-1 levels individually during the first 72 hours post-randomisation.

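### The primary endpoint is defined inconsistently (marker and start of the window), so readings taken before the first dose can enter the constant-effect estimate and dilute it

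*Combined protocol and SAP*

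**What the plan says.** On the marker, Section 2.4.1 says "we have chosen to use a measure of circulating maternal serum levels of sFlt-1 and sEng as primary endpoints", and the end of that section frames the hypothesis as suppression of both. Section 8.1 defines the primary outcome through "maternal serum sFlt-1 levels individually during the first 72 hours post-randomisation", with no mention of sEng. Sections 9.1 and 9.2 also use sFlt-1 alone.

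On the time window, Section 8.1 counts from randomisation. Section 9.1 sizes the trial on a difference "during the first 72 hours after onset of treatment". Section 9.2 opens with "The primary outcome measure of sFlt-1 during the first three days" and gives no origin. Section 6.6.1 says "samples need to be collected daily at baseline, on days 1-3 of the trial treatment period", without defining day 1.

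On dosing and sampling times, Section 6.2.2 places the daily dose in the evening, starting on the day of randomisation, but adds: "If a patient is randomised too late in the evening, the first dose may be given the following evening". Section 6.6.1 ties blood draws to routine sampling where possible and sets no hour.

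On the model, Section 9.2 specifies a repeated measures analysis adjusted for baseline and states: "For the primary analysis the treatment effect will be considered constant over time". A trend over time is left to secondary analyses.

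**The concern.** Two questions have to be settled before any analysis: which marker is primary, and when the window starts. The sections answer them differently.

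The second question affects the numbers directly. If the window starts at randomisation and the first capsule is taken the following evening, about 24 of the 72 hours pass before any drug. A routine blood sample in that time is an outcome reading under Section 8.1, although pravastatin cannot have acted. No rule moves it to baseline, and the model treats the effect as equal on all three days.

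The result is an estimate biased towards zero and some loss of power. The bias matters beyond the test, because Section 2.6 says this trial will establish the effect of pravastatin on these factors as groundwork for a substantive trial.

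**Working it through.** **1. Reproduce the plan's sample size.** Inputs from Section 9.1: difference 1 SD, 80% power, p<0.05, three daily readings, ICC 0.9, correlation with baseline 0.1. Two-sided tests are from Section 9.2 and equal allocation from Section 5.3.

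- Single time point, exact two-sided t-test: 34 in total (power 0.807). This matches the stated 34.
- Variance factor for the mean of three readings adjusted for baseline: [1 + (3 − 1) × 0.9]/3 − 0.1² = 0.9333 − 0.01 = 0.9233.
- 34 × 0.9233 = 31.4, rounded up to an even 32. This matches the stated 32.

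**2. When can a day-1 reading precede the first dose?** Take a woman randomised late in the evening, first dosed the next evening, with a routine draw during the day in between.

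- Day 1 counted from randomisation (Section 8.1): that draw is an outcome reading and is pre-dose.
- Day 1 as the calendar day of the first dose (one reading of Section 6.6.1): again outcome and pre-dose.
- Day 1 as the day after the first dose (another reading of Section 6.6.1): the first outcome draw follows the dose, and there is no dilution.

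Late randomisation is possible, since Section 5.2 offers it online around the clock. How often it happens is not stated.

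**3. Size of the dilution.** Let f be the share of women whose day-1 reading is pre-dose (an assumption, 0 to 1). With complete data and the exchangeable correlation used in Section 9.1, each reading has weight one third, so the average effect is δ × (1 − f/3). Power uses the noncentral t with N − 2 degrees of freedom and noncentrality (average effect/√0.9233) × √(N/4). Worked case, δ = 1 SD, f = 1, N = 32: 0.667/0.961 × √8 = 1.96, giving power 0.476.

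| f | Average effect, δ = 1 SD | Power, N=32 | Power, N=64 |
|---|---|---|---|
| 0 | 1.00 SD | 81% | 98% |
| 0.5 | 0.83 SD | 66% | 93% |
| 1 | 0.67 SD | 48% | 78% |

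The halving expected in Section 9.1 is 33.3/26.4 = 1.26 SD. With f = 1 this becomes 0.84 SD, with power 67% at N=32 and 93% at N=64.

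**4. Type I error.** With no drug effect, the true difference is zero on every day, so averaging over days cannot create one. A simulation of the baseline-adjusted test under the null (20,000 trials each) rejected in 5.0% at N=32 and 5.2% at N=64. The simulation error is √(0.05 × 0.95/20,000) = 0.15 percentage points, so both agree with 5%.

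**5. Would leaving out day 1 cost much?** For days 2-3 the variance factor is (1 + 0.9)/2 − 0.01 = 0.94, and 34 × 0.94 = 31.96, again 32. Power at 1 SD and N=32 is 81%, provided the data are complete and the full effect is present by day 2.

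**The case against.** The strongest defence is that pre-dose outcome readings are not the planned case. Section 6.6.1 lists baseline apart from days 1-3 and counts in treatment days. With a first dose on the evening of randomisation, a pre-dose day-1 sample would repeat baseline on the same date, so the natural reading is that day 1 is the next day. The delayed dose is an exception, and under a treatment clock the sampling days would move with it. This stands to the extent that f is probably well below 1. It does not help Section 8.1, which counts from randomisation, and the protocol nowhere defines day 1.

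The maximum of 64 also absorbs most of the power loss if data are largely complete. That is true, but Section 9.1 assigns the increase to women who do not provide all three days, and a larger sample does not remove bias. The secondary time-trend analysis and plots might reveal a weak day 1, but they leave the primary estimate as it is. Section 9.2 defers detail to a separate Statistical Analysis Plan, which is not in the text reviewed; the protocol's conflicting definitions would still need reconciling.

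A reader might infer more than the documents support:

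- *That type I error is uncontrolled.* The constant-effect model does not inflate it (step 4), and no outcome, sample-size or analysis section tests sEng as primary. Only if sEng were also tested at an unadjusted 5% would the familywise error rise: to 9.75% for independent markers, 7.0% at correlation 0.9, and never above 10%.
- *That sEng is never analysed.* Table 1, the table of secondary outcomes, lists it, and Section 9.2 extends its methods to the remaining continuous measures.
- *That there are three clocks.* There are two origins, randomisation and start of treatment, plus one phrase with no origin.
- *That power is 48%.* That figure needs N=32 and every day-1 sample taken before the dose.
- *That day 1 should leave the primary estimate.* This would drop women with only a day-1 reading, in a trial that expects missing days, and Section 9.1 cites inhibition within 24 hours ex vivo.

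**Conclusion.** The point holds as an inconsistent definition with a conditional cost. The marker conflict and the conflict between the two window origins are in the current text and do not depend on any assumption. The dilution depends on f, which the documents do not give. The estimate shrinks by the fraction f/3, which is nothing if day 1 follows the first dose for everyone and one third at the extreme, whatever the sample size. At 1 SD with complete data, power lies between 81% and 48% at N=32 and between 98% and 78% at N=64. These figures rest on the plan's ICC and baseline correlation, equal weight for each day, zero effect before the first dose and full effect on every later reading. The single sFlt-1 test keeps its 5% type I error.

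**What to change.** - Amend Section 2.4.1 so that sFlt-1 is the only primary marker, as in Sections 8.1, 9.1 and 9.2, and name sEng in the Section 8.2 list with the same model. If both are meant to be primary, state a multiplicity rule instead. With 0.025 each, the normal approximation gives 4 × (2.241 + 0.842)² × 0.9233 = 35.1, or 36 in total, so 64 would still suffice with largely complete data.
- Use one window origin in Sections 6.6.1, 8.1, 9.1 and 9.2. Number sampling days from the first blinded dose, or from randomisation for a woman never dosed, so that she stays in the intention-to-treat analysis.
- Record the time of each draw and each dose. Section 6.6.1 asks only for the sample date on the label.
- Treat any sample taken before the first dose as baseline, never as outcome, and say which one is the covariate if there are two.
- Keep days 1-3 as the primary window, with the average over days 2-3 as a sensitivity analysis.

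The cost is protocol wording, two extra form fields, and a few readings reclassified as baseline.
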